# **Overview**

## **Schema**

Patients scheduled to undergo gastrectomy with D2 lymph node dissection for advanced gastric cancer will be enrolled.

・Age between 20 and 80 years / ・Performance status (PS) of 0 or 1

Written informed consent will be obtained preoperatively

Patient Registration

Patients with negative intraoperative peritoneal cytology will be excluded.

During surgery, peritoneal lavage cytology and

stamp cytology will be performed.

Patients with a positive result in any of the intraoperative cytology tests will be eligible for enrollment.

During surgery, before abdominal closure,

the peritoneal cavity will be lavaged with 12 liters of normal saline.

Follow-up period: 3 years postoperatively

<<B群

手術中、閉腹前に2Lの生理食塩水で腹腔内洗浄

## **Background**

- Peritoneal recurrence is common even in patients with **gastric cancer who have undergone curative resection**.
- **Peritoneal lavage cytology** has traditionally been used to predict peritoneal recurrence; however, its **low sensitivity** remains a concern. Previous studies at our institution have shown that **adding imprint cytology** can improve the sensitivity of detection.
- Typically, the peritoneal cavity is lavaged with approximately **2 liters of normal saline** after gastrectomy. Some reports suggest that **extensive intraoperative peritoneal lavage with normal saline** in patients with positive peritoneal cytology may improve survival outcomes.
- However, to date, **no prospective studies** have investigated the impact of extensive intraoperative peritoneal lavage on **recurrence-free survival** in patients with positive peritoneal or imprint cytology.

## **Objectives**

　This non-randomized Phase II study aims to evaluate the efficacy of extensive intraoperative peritoneal lavage on recurrence-free survival in patients scheduled to undergo gastrectomy with D2 lymph node dissection who have positive intraoperative peritoneal cytology or positive gastric wall imprint cytology.

In addition, data regarding safety and feasibility will be collected as secondary endpoints.

Primary endpoint: Recurrence-free survival

Secondary endpoints: ① Overall survival, ② Sites of postoperative recurrence, ③ Incidence of postoperative adverse events

## **Patients**

1. Histologically confirmed gastric cancer from the primary gastric lesion by endoscopic biopsy, including one of the following types: papillary (pap), well-differentiated tubular (tub1), moderately differentiated tubular (tub2), poorly differentiated (por1, por2), signet-ring cell (sig), mucinous (muc), or other special types.
2. Positive intraoperative peritoneal cytology or gastric wall imprint cytology, with no evidence of distant metastasis. Patients must be candidates for R0/1 gastrectomy with D2 lymph node dissection (total or distal gastrectomy, including laparoscopic procedures). General anesthesia with or without epidural anesthesia will be used.
3. Esophageal invasion of 3 cm or less, with no thoracotomy required.
4. Age between 20 and 80 years.
5. ECOG performance status of 0 or 1.
6. No prior chemotherapy (including endocrine therapy) or radiotherapy for other malignancies.
7. Adequate organ function, confirmed within 56 days prior to enrollment (tests performed on the same day of the week up to 8 weeks before enrollment are acceptable):

- White blood cell count: 3,000–10,000 /mm³
- Platelet count ≥ 100,000 /mm³
- AST ≤ 100 IU/L, ALT ≤ 100 IU/L
- Total bilirubin ≤ 2.0 mg/dL
- Serum creatinine ≤ 1.5 mg/dL

1. Written informed consent obtained from the patient.

## **Treatment**

Surgery will be performed according to the Japanese Gastric Cancer Treatment Guidelines (3rd edition, for physicians), including D2 or more extensive lymph node dissection.

During the operation, the peritoneal cavity will be lavaged with 12 liters of normal saline prior to abdominal closure.

## **Planned Sample Size and Study Duration**

- Planned number of eligible patients: 65
- Enrollment period: 2 years
- Follow-up period: 3 years after completion of enrollment
- Total study duration: 5 years

# **Background**

The mortality rate of gastric cancer in Japan has continued to decline in both men and women since the 1970s, and in men, lung cancer surpassed gastric cancer as the leading cause of cancer-related death after 1993; however, gastric cancer remains the second leading cause of death from malignant neoplasms in Japan¹. According to the Japanese Gastric Cancer Treatment Guidelines (3rd edition), standard surgery for tumors with N(+) involvement or T2 or deeper is either distal gastrectomy or total gastrectomy. Total gastrectomy is indicated when an adequate resection margin cannot be secured by distal gastrectomy. Regarding lymph node dissection for advanced gastric cancer, based on the results of the JCOG9501 trial conducted in Japan, D2 lymphadenectomy is considered the standard treatment. Concerning adjuvant therapy after curative resection, based on the results of the ACTS-GC trial (Adjuvant Chemotherapy Trial of S-1 for Gastric Cancer), postoperative administration of S-1 for one year has become the standard treatment in Japan for patients with stage II–IIIB gastric cancer (excluding pT1)². Furthermore, following the results of the randomized phase III trial (CLASSIC trial) comparing surgery alone with adjuvant chemotherapy using capecitabine plus oxaliplatin (CapeOX), CapeOX therapy is also recommended as a postoperative adjuvant chemotherapy option³.
 These treatment developments have improved the survival outcomes of patients undergoing gastric cancer surgery. However, even after curative resection, peritoneal recurrence has been reported in 37–39.4% of cases (JCOG9206-1, JCOG9206-2, JCOG9501 trials). In all these trials, the most common site of recurrence after curative resection was the peritoneum. In the ACTS-GC trial, peritoneal recurrence occurred in 14.6% (77/549) of patients even with adjuvant chemotherapy⁴. These findings indicate that even among cases currently judged as curatively resected by staging, there are high-risk patients for peritoneal dissemination recurrence.
 At present, peritoneal cytology (CY) is the most widely used method to predict peritoneal dissemination recurrence. The 5-year overall survival rate for CY-positive cases has been reported to be approximately 0–2%, indicating an extremely poor prognosis. This highlights the need for novel treatment development to improve outcomes in this patient population^⁵,⁶^.
However, the current problem with CY is its low sensitivity in predicting recurrence. In a previous study conducted at our institution, the sensitivity increased from 25.0% to 47.1% when imprint cytology was used in combination with standard CY. Considering the importance of including as many high-risk patients as possible in novel treatment development, it is necessary to advance new therapies even for patients who are positive on imprint cytology.
 In the past, small-scale randomized controlled trials have been conducted targeting CY-positive cases to examine the efficacy of gastrectomy combined with extensive intraoperative peritoneal lavage (EIPL) and intraperitoneal chemotherapy⁷. Among these, the combination of EIPL and intraperitoneal chemotherapy showed the best outcomes, but even EIPL alone was more effective than surgery alone. Furthermore, in single-arm studies, EIPL has been reported to achieve a 5-year survival rate of 46.5% in CY1P0 cases, suggesting that EIPL alone may contribute to recurrence prevention⁸. However, no prospective trial has examined the effect of EIPL on survival in CY-positive or imprint cytology-positive cases.
 In previous reports, 10 liters of peritoneal lavage were performed. At our institution, 2 liters are typically used at the end of surgery. Therefore, in this trial, we set the intervention to evaluate the effect of an additional 10 liters of lavage (total 12 liters) compared with the standard method. Performing extensive intraoperative lavage immediately before the end of surgery is unlikely to cause severe adverse events, and this intervention can be easily implemented regardless of the institution. Based on these considerations, we designed a non-randomized phase II trial to evaluate the superiority of 12-liter peritoneal lavage in terms of recurrence-free survival in patients who are CY-positive or imprint cytology-positive.

## **Significance of This Study**

The standard treatment for advanced gastric cancer is gastrectomy with D2 lymphadenectomy followed by adjuvant chemotherapy; however, the frequency of postoperative recurrence remains substantial, highlighting the need for further therapeutic development. In particular, overcoming the high incidence of peritoneal recurrence is a critical challenge, and evaluating the efficacy of extensive intraoperative peritoneal lavage in this study is therefore considered meaningful.

## **Ancillary Studies**

In this study, subgroup analyses are planned for patients with positive peritoneal cytology and positive imprint cytology. Additionally, since intraoperative blood loss and transfusion volume have been reported to be associated with recurrence, these data will also be examined. Samples obtained by scraping the gastric wall during surgery will be used to investigate the relationship between gene expression in the scraped cells, clinicopathological factors, and prognosis.
 For any future ancillary studies using data from this trial, the proposed study plan must be documented and submitted to the principal investigator. The principal investigator will review the proposed study content and methodology together with the proposer.

# **Overview of Investigational Product**

## **Investigational Product**

Normal saline (sodium 154 mEq/L, chloride 154 mEq/L) will be used.

## **Expected Adverse Reactions and Device Malfunctions**

No adverse events have been reported with intraperitoneal use of the above solution. However, large intravenous doses may cause electrolyte disturbances, congestive heart failure, edema, or acidosis.

# **Diagnostic Criteria, Staging, and Classification of Target Disease**

## **Gastric Cancer Guidelines**

Terminology and classification in this protocol follow the 14th edition of the Japanese Gastric Cancer Classification and the 3rd edition of the Japanese Gastric Cancer Treatment Guidelines.

## **Performance Status (PS) Assessment**

The Japanese translation of the ECOG scale will be used:

| Grade | | Performance Status |
| --- | --- | --- |
| 0 | Asymptomatic, fully active, able to carry out all pre-disease activities without restriction. | |
| 1 | Mild symptoms, restricted in physically strenuous activity but ambulatory and able to do light work (e.g., light housework, office work). | |
| 2 | Ambulatory and capable of self-care but unable to perform work activities; up >50% of waking hours. | |
| 3 | Limited self-care, often requires assistance; confined to bed/chair >50% of waking hours. | |
| 4 | Completely disabled, requires constant care, confined to bed. | |

# **Eligible Patients**

Patients who meet all inclusion criteria and none of the exclusion criteria will be considered eligible. Staging and histological classification follow the 14th edition of the Japanese Gastric Cancer Classification.

## **Inclusion Criteria**

1) Histologically confirmed gastric cancer by endoscopic biopsy (pap, tub1, tub2, por1, por2, sig, muc, or special types).

2) Positive peritoneal cytology or imprint cytology, no other distant metastasis, and R0/1 resection feasible via D2 gastrectomy (total or distal, including laparoscopic), under general ± epidural anesthesia.

3) Esophageal invasion ≤3 cm; no thoracotomy required.

4) Age 20–80 years.

5) ECOG PS 0–1.

6) No prior chemotherapy (including endocrine therapy) or radiotherapy for other cancers.

7) All of the following criteria must be met. (The latest preoperative laboratory values within 56 days before enrollment will be used. Tests performed on the same day of the week 8 weeks prior to enrollment are acceptable.)

① White blood cell count: 3,000–10,000/mm³

② Platelet count ≥100,000/mm³

③ AST ≤100 IU/L, ALT ≤100 IU/L

④ Total bilirubin ≤2.0 mg/dL

⑤ Serum creatinine ≤1.5 mg/dL

8) Written informed consent for study participation has been obtained from the patient.

［Rationale］

1) To ensure that the case is histologically confirmed as gastric cancer.

2) Patients with positive peritoneal cytology or imprint cytology are considered high-risk for peritoneal recurrence and are therefore eligible. However, patients with other distant metastases are often unable to achieve R0/1 resection and are excluded from this study.

3) Patients with esophageal invasion ≥3 cm may require thoracotomy and are excluded.

4 -7) Special cases or patients with poor preoperative general condition are excluded.

8) Patient consent is mandatory.

## **Exclusion Criteria**[**^9^**](#_ENREF_9)

1) Pregnant or breastfeeding women.

2) Psychiatric disorders interfering with participation.

3) Continuous systemic steroid use.

4) Myocardial infarction within 6 months or unstable angina.

5) Uncontrolled hypertension.

6) Insulin-treated or uncontrolled diabetes.

7) Respiratory disease requiring continuous oxygen.

［Rationale］

1)〜7) To ensure the validity of efficacy evaluation and to consider patient safety. These criteria were set in accordance with previous clinical trials in gastric cancer cases.[^9^](#_ENREF_9)

# **Patient Registration**

## **Registration Procedure**

**Eligible Patients:** Prior to surgery, the principal investigator or sub-investigator will obtain written informed consent. If the patient meets all inclusion criteria (except criterion 2) and none of the exclusion criteria, the case registration form will be completed and the patient will be enrolled in the study.

**Analysis Population:** If intraoperative findings confirm that the patient meets the eligibility criteria, the eligibility confirmation form will be completed, and the protocol treatment will be administered. The case registration form and eligibility confirmation form will be stored at the study office. Any withdrawal of consent, discontinuation, or dropout must be reported promptly.

# **Study Design**

## **Type and Design**

This is a single-arm, non-randomized phase II study to evaluate the superiority of extensive intraoperative peritoneal lavage for recurrence-free survival in patients undergoing D2 gastrectomy with positive intraoperative peritoneal or imprint cytology. For setting the threshold, survival outcomes of 138 eligible patients operated at our department from 1997 to 2012 were used.

**Rationale:** The target population is rare, and patient accrual may require considerable time. Therefore, a randomized controlled trial is considered difficult, and this single-arm phase II study uses historical outcomes to set thresholds.

## **Clinical Hypothesis and Sample Size Determination**

1. **Clinical Hypothesis:**

Extensive intraoperative peritoneal lavage may prolong recurrence-free survival in patients with positive intraoperative peritoneal or imprint cytology after D2 gastrectomy.

1. **Sample Size Determination:**

The median recurrence-free survival of CY- or imprint-positive patients operated at our hospital from 1997 to 2012 was 315 days (0.86 years). This value was set as the threshold, and the expected median RFS with the study intervention is 438 days (1.2 years). Assuming α=0.05 and β=0.20, 62 patients are required. The planned enrollment is 65 patients.

## **Accrual Plan**

In 2011, 20 patients met eligibility criteria at Osaka City University Hospital. Assuming a 75% consent rate, 15 patients per year are expected. Single-center accrual is insufficient for timely completion; therefore, this study will be conducted as a multicenter trial. With participation from institutions expected to enroll 5–15 patients per year, total annual accrual is estimated at approximately 35 patients. The enrollment period will be 2 years. A 3-year follow-up period after enrollment completion is required, making the total study duration 5 years.

## **Outline of the Study**

| Consent acquisition | ⇨ | Registration | ⇨ | Preoperative examination at the start of surgery | ⇨ | Eligibility confirmation |  |  |  | Postoperative follow-up for 3 years Blood tests (every 3 months) CT (every 6 months) Upper gastrointestinal endoscopy (once a year) |
| --- | --- | --- | --- | --- | --- | --- | --- | --- | --- | --- |
|  |  |  |  |  |  |  | ⇨ |  |  |  |
|  |  |  |  |  |  |  |  | Intraoperative extensive peritoneal lavage at the end of surgery |  |  |
|  |  |  |  |  |  |  | ⇨ |  |  |  |
|  |  |  |  |  |  |  |  |  |  |  |

## **Study Participation Period for Subjects**

## All subjects will be followed up for 36 months postoperatively. Follow-up will be conducted at outpatient visits every 3 months (maximum 12 visits within 36 months).

## **Dosage, Administration, and Duration of Study Drug**

Intraoperative extensive peritoneal lavage will be performed using 12 L of physiological saline at the end of surgery.

## **Regulations on Concomitant Medications (Therapies)**

1) Concomitant medications (therapies): None

2) Prohibited concomitant medications (therapies): None

## **Handling and Dispensing of Study Drug**

The drugs used in this study are those routinely stocked in the surgical department.

## **Post-Trial Care**

## After the study, efforts will be made to ensure that subjects receive the best possible preventive, diagnostic, and therapeutic care based on the results of the study.

## **Storage and Use of Samples for Other Institutions**

Samples obtained for imprint cytology in relation to this study will be stored in the Department of Molecular Oncology for 5 years after the study report is completed. The study office is responsible for management and will report the management status to the hospital director. Disposal of samples will be conducted in an anonymized state.
 Researchers will be instructed and supervised to ensure the accuracy of information and samples obtained from humans, which will also be stored for 5 years after study completion under secure management to prevent leakage, mix-up, theft, or loss.

# **Observations and Examinations, Schedule**

## **8-1　Pre-Registration Assessment Items**

**To be performed within 56 days prior to registration:**

1) General condition: PS (ECOG), height, weight

2) Peripheral blood count: WBC, hemoglobin, platelet count

3) Blood biochemistry: AST, ALT, total bilirubin, creatinine, CRP

4) Tumor markers: CEA, CA19-9

5) Contrast-enhanced CT of upper abdomen and pelvis (slice thickness ≤ 10 mm; if contrast CT is not possible due to allergy, non-contrast CT is acceptable)

6) Upper gastrointestinal endoscopy (histopathological examination)

7) Chest X-ray (one direction): lung field condition

8) Resting 12-lead ECG

9) Pulmonary function test: FEV1.0%, %VC

## **Intraoperative and Postoperative Assessment Items**

**8-2-1 Surgical Assessment Items**

1. Surgical procedure, reconstruction method
2. Operative time
3. Blood loss (from incision to closure), transfusion volume (intraoperative and until first discharge)
4. Primary tumor site
5. Tumor size
6. Depth of invasion (post-resection), lymph node metastasis (post-resection), surgical stage (post-resection)
7. Omentectomy
8. Intraoperative complications (CTCAE v3.0 Short Name and JCOG intraoperative/postoperative complication criteria): from incision to closure. The attending physician's judgment regarding causality with the treatment will also be reported.

􀂂 Intraoperative/postoperative complication criteria: pulmonary embolism, lung infarction

􀂂 Surgical/intraoperative injury: pancreas, spleen, gallbladder-common bile duct, portal vein, major arteries of organs, major veins of organs, esophagus, duodenum, jejunum, ileum, colon

􀂂 Other fatal complications

**8-2-2 Postoperative In-Hospital Assessment Items**

1) Early postoperative complications (CTCAE v3.0 Short Name, JCOG intraoperative/postoperative complication criteria, Clavien-Dindo classification) up to 90 days postoperatively.

􀂂 Assessment items: pancreatic fistula, postoperative bleeding, intra-abdominal abscess, gastrointestinal anastomotic leakage, gastrointestinal stricture, cholecystitis, dumping syndrome, delayed gastric emptying, reflux esophagitis, obstructive ileus, paralytic ileus, thrombosis/embolism, postoperative pneumonia, pleural effusion, chylous ascites, surgical site infection, wound dehiscence, other Grade ≥3 non-hematological toxicities

2) Date of first discharge after surgery

**8-2-3 Postoperative Assessment Items**

1) Pathological findings

􀂂 Histological type of primary lesion

􀂂 Depth of invasion, lymph node metastasis

􀂂 Proximal and distal margins

􀂂 Histopathological stage, overall curability

􀂂 Details of each lymph node metastasis

2) Recurrence status

􀂂 Regular follow-up as described below will be conducted to assess recurrence by the attending physician or study office. Recurrence sites will also be recorded.

- 1. Tumor markers (CEA, CA19-9): every 3 months for 3 years postoperatively
  2. CT of upper abdomen and pelvis: every 6 months for 3 years postoperatively
  3. Upper gastrointestinal endoscopy: once a year only for distal gastrectomy

Schedule Table

| Item | Pre-op | Post-op Observation Period | | | | | | | | | | | |
| --- | --- | --- | --- | --- | --- | --- | --- | --- | --- | --- | --- | --- | --- |
| Time | 2–4 weeks before | 3M | 6M | 9M | 1Y | 1Y  3M | 1Y  6M | 1Y  9M | 2Y | 2Y  3M | 2Y  6M | 2Y  9M | 3Y |
| Consent acquisition | ● |  |  |  |  |  |  |  |  |  |  |  |  |
| Patient background | ● |  |  |  |  |  |  |  |  |  |  |  |  |
| Subjective/objective symptoms | ● | ● | ● | ● | ● | ● | ● | ● | ● | ● | ● | ● | ● |
| Adverse events observation ^a^ |  | ● | ● | ● | ● | ● | ● | ● | ● | ● | ● | ● | ● |
| Upper GI endoscopy | ● |  |  |  | ● |  |  |  | ● |  |  |  | ● |
| CT scan | ● |  | ● |  | ● |  | ● |  | ● |  | ● |  | ● |
| Hematology tests ^b^ | ● | ● | ● | ● | ● | ● | ● | ● | ● | ● | ● | ● | ● |
| Biochemistry tests ^c^ | ● | ● | ● | ● | ● | ● | ● | ● | ● | ● | ● | ● | ● |
| Physiological function tests | ● |  |  |  |  |  |  |  |  |  |  |  |  |

M: Month、Y: Year

a: Adverse events include all undesirable events, regardless of causality with the drug.

b: Hematology tests include WBC, hemoglobin, platelet count; used to confirm safety.

c: Biochemistry tests include TP, albumin, AST, ALT, total bilirubin, creatinine, CRP, CEA, CA19-9; used to confirm safety and treatment effect.

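### Two rules for recording adverse events disagree on unlisted Grade 1–2 events, and the four reactions the protocol names for saline fall in that gap

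*Protocol*

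**What the plan says.** **Recording rules.** Protocol section 9.1 (Response to Subjects for Adverse Events) defines an adverse event broadly and has the investigator enter each recognised one in the medical record and the CRF. It sets no grade limit. Footnote a of the Schedule Table in 8-2-3 is equally broad: "Adverse events include all undesirable events, regardless of causality with the drug". Section 13.3 (Safety Analysis) is narrower. Events specified in section 8.2 get a grade and onset date on the CRF, and all others are entered as free text only from Grade 3 upwards.

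**Listed events.** Section 8-2-1 covers the operation, with "Intraoperative/postoperative complication criteria: pulmonary embolism, lung infarction", a list of injured organs and vessels, and other fatal complications. Section 8-2-2 covers early complications "up to 90 days postoperatively" and ends with "chylous ascites, surgical site infection, wound dehiscence, other Grade ≥3 non-hematological toxicities".

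**Named reactions to saline.** Section 2.2 says "No adverse events have been reported with intraperitoneal use of the above solution", and adds that "large intravenous doses may cause electrolyte disturbances, congestive heart failure, edema, or acidosis".

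**Laboratory panels.** Before registration: "Blood biochemistry: AST, ALT, total bilirubin, creatinine, CRP". In the Schedule Table, footnote c: "Biochemistry tests include TP, albumin, AST, ALT, total bilirubin, creatinine, CRP, CEA, CA19-9; used to confirm safety and treatment effect". Blood counts and tumor markers complete the tests.

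**Use.** How often adverse events occur after surgery is the third secondary endpoint (section 11.2). Section 15.5 has safety data reviewed twice a year against the expected range.

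**The concern.** A count of adverse events needs one rule for what is counted. Here a Grade 1–2 event that is not on the 8.2 lists must be entered under 9.1 and is left out under 13.3. The trial is multicenter (section 6.3), so two sites can each follow the protocol and produce different counts from the same events. A later analysis plan cannot repair this, because an event that never reached the CRF cannot be recovered.

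The gap includes the only reactions that the protocol itself names for the study fluid. A final report that no such reaction occurred after 12 L of lavage would be firm for Grade 3 or higher events noticed in care. For milder ones it would be unclear whether they were absent or simply not entered.

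**Working it through.** The protocol gives no figure to reproduce here, and no sample size or power calculation bears on the point. The check sets the sections side by side.

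**Step 1: the two rules by type of event.**

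| Event | Section 9.1 | Section 13.3 | Agree? |
| --- | --- | --- | --- |
| Listed in 8.2, Grade 1–2 | enter | enter | yes |
| Listed in 8.2, Grade ≥3 | enter | enter | yes |
| Not listed, Grade ≥3 | enter | enter (free text) | yes |
| Not listed, Grade 1–2 | enter | do not enter | **no** |

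One of the four cells conflicts. The last item of 8-2-2 sides with 13.3, since it admits unlisted non-hematological toxicities only from Grade 3. Footnote a shares the breadth of 9.1, but it describes what is observed and does not itself set a CRF rule.

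**Step 2: are the four section 2.2 reactions listed?**

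- 8-2-2 names 17 complications. Matches with electrolyte disturbance, congestive heart failure, edema or acidosis: 0.
- 8-2-1 names 2 complications and 11 injury sites. Matches: 0.
- Pleural effusion, which could accompany fluid overload, is in 8-2-2 without a grade limit, but it is not one of the four.

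All four are therefore unlisted, and their Grade 1–2 forms fall in the conflicting cell. For example, mild edema on the second day after surgery is entered under 9.1 and omitted under 13.3. A mild pleural effusion on the same day is entered under both.

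**Step 3: would scheduled tests show them anyway?**

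- The pre-registration list has 10 blood tests: 3 blood counts, 5 biochemistry tests and 2 tumor markers.
- Footnotes b and c have 3 + 9 = 12: the same 10 plus total protein and albumin.
- Distinct tests: 12. Electrolyte or acid-base measures among them: 0.
- The first scheduled postoperative sample is at 3 months.

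Early laboratory changes would be seen only if ordinary care looked for them.

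**Step 4: what is captured regardless?**

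- Grade ≥3: the last item of 8-2-2 and the free-text rule of 13.3.
- Serious events during surgery or the postoperative hospital stay: section 9.2, whatever the cause.
- Fatal intraoperative events: the last item of 8-2-1.

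**Step 5: CTCAE version.** Sections 8-2-1 and 8-2-2 cite v3.0, while 13.3 grades by v4.02. Any item added to the lists would fall under two versions unless this is settled too.

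**The case against.** The best defence is that 13.3 is the specific rule. It names the form and the fields, and 8-2-2 agrees with it. Section 9.1 is mainly about clinical response, and it carries text that cannot apply to a single-arm trial, such as disclosure of a subject's allocation. A site could sensibly follow 13.3. The fields of the postoperative and progress forms are not shown and may settle the matter in practice. This has force: the text supports saying that events could be recorded unevenly, not that they will be. But the protocol nowhere says that 13.3 limits 9.1, so the contradiction stands.

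Three stronger readings are tempting, and the protocol supports none of them.

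- **Lavage is expected to cause these four reactions.** A reader might infer this from the title of section 2.2. The section ties them to large intravenous doses and reports none by the intraperitoneal route, and no figure is given for absorption of the 12 L. They are a possibility to check.
- **Important harm would be missed.** Step 4 of the working shows that Grade ≥3 events and serious in-hospital events have a route into the records.
- **Leaving out electrolytes is an error that calls for new scheduled tests.** Given the low risk argued in the Background and section 15.5, that panel is a defensible choice. A pre-registration value may be 56 days old and could not measure an acute shift. The protocol mentions no routine test on the first postoperative day.

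**Conclusion.** The contradiction is real but minor. Unlisted Grade 1–2 events have two incompatible recording rules, so the adverse event endpoint has no single definition for them. All four reactions named in section 2.2 are unlisted and share this problem in their milder forms.

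The size cannot be put in events or percentages, because the protocol gives no rate for these reactions and no indication of which rule sites follow. A reader might try to size the gap with the upper confidence bound for zero events in 65 patients. That bound would describe Grade ≥3 events, which are captured, and says nothing about the milder ones. The effect is confined to one descriptive secondary endpoint and the twice-yearly safety review. Recurrence-free survival and its decision rule are unaffected.

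The conclusion rests on two assumptions: that the CRFs, which are not shown, do not already impose one rule, and that no other part of the protocol ranks 13.3 above 9.1. None was found.

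**What to change.** 1. **One recording rule**, stated alike in 9.1, 13.3 and footnote a of the Schedule Table: all grades go in the CRF for events listed in 8.2, and Grade ≥3 for all others.
2. **Four additions to the 8-2-2 list**: electrolyte disturbance, acidosis, edema and heart failure, at all grades as noticed in care. Section 13.3 then already requires a grade and onset date for them.
3. **One CTCAE version**: v4.02, as in 13.3, for the whole of section 8.2 in place of v3.0.

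Optional: copy postoperative sodium, potassium and chloride to the CRF where care already draws them, and report them with the number of patients tested as the denominator. No new scheduled test or visit is needed.

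The cost is a few protocol lines, four CRF items and a little data entry. Two limits remain. Mild events will be seen only when care looks for them. With no control arm, they could reflect anesthesia, intravenous fluids or transfusion as well as lavage, so they should be reported descriptively.
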